## Abstract

**Background:**

Osteoarthritis is a destructive joint disease that leads to degeneration of cartilage and other morphological changes in the joint. No medical treatment currently exists that can reverse these morphological changes. Intra-articular injection with autologous, micro-fragmented adipose tissue has been suggested to relieve symptoms.

**Methods/Design:**

The study is a blinded randomized controlled trial with patients allocated in a 1:1 ratio to 2 parallel groups. Patients suffering from pain and functional impairment due to osteoarthritis Kellgren-Lawrence grades 2–3 in the tibiofemoral joint are eligible for inclusion. The intervention group is treated with an intra-articular injection with autologous, micro-fragmented adipose tissue prepared using the Lipogems® system. The control group receives an intra-articular injection with isotonic saline. In total, 120 patients are to be included.

The primary outcome is The Knee injury and Osteoarthritis Outcome Score (KOOS4) evaluated at 6 months. Secondary outcomes are KOOS at 3, 12 and 24 months; the Tegner activity score; treatment failure; and work status of the patient. The analysis will be conducted both as intention-to-treat and per-protocol analysis.

**Discussion:**

This trial is the first to investigate the efficacy of autologous, micro-fragmented adipose tissue in a randomized controlled trial. The study uses the patient-reported outcome measure Knee Injury and Osteoarthritis Outcome Score (KOOS4) after 6 months as the primary outcome, as it is believed to be a valid measure to assess the patient’s opinion about their knee and associated problems when suffering from osteoarthritis.

## Administrative information

Note: the numbers in curly brackets in this protocol refer to SPIRIT checklist item numbers. The order of the items has been modified to group similar items (see http://www.equator-network.org/reporting-guidelines/spirit-2013-statement-defining-standard-protocol-items-for-clinical-trials/).

## Introduction

### Background and rationale {6a}

Osteoarthritis (OA) of the knee is a destructive joint disease, seen with increasing age, causing degeneration of cartilage, damage to the underlying bone and morphological changes to the joint [1]. It is a major public health concern due to the increased life expectancy of the ageing population [2, 3]. No approved medical treatment currently exists that reverses the morphological changes. Conventional treatment includes physiotherapy, pain medicine, braces and in end-stage OA surgical knee replacement [4].

During the past decade, researchers have started to explore the regenerative potential of mesenchymal stem cells (MSC) in OA [5]. MSCs are multipotent progenitor cells able to give rise to osteocytes, adipocytes, chondrocytes, myoblasts and tenocytes [6]. MSCs were first used to treat Chondral defects in 1998 [7] and to treat OA in 2002 [8]. Since then, a number of case reports and prospective series have been published showing significant short- and long-term effects on pain and cartilage thickness [5]. Recently, a prospective case-series of 1128 patients involving 1856 joints found an improvement of at least 50% in 86% of patients at 3 months and 91% of patients at 12 months using a modified Knee/Hip Osteoarthritis Outcome Score (KOOS/HOOS) questionnaire. Only 0.9% of patients did not show improvement after treatment [9]. However, when interpreting these studies, one should bear in mind that they include no controls and are level-four evidence and as such prone to bias.

No serious adverse effects like infection or neoplastic formation have been observed in treatment of OA with MSC [9, 10]. Non-manipulated or minimally manipulated cell therapies have been used within a wide range of medical conditions including stroke, myocardial infarction, Crohn’s disease, rheumatoid arthritis and breast augmentation. More than 17,000 scientific articles have been published reporting treatment of more than 320,000 patients [11]. No severe safety issues have been raised [12].

Mesenchymal stem cells can be derived from bone marrow or adipose tissue [5]. Most research has been performed on bone marrow-derived stem cells. Studies have shown promising results, but in 2016 a randomized study found no effect of active treatment with bone marrow aspirate concentrate compared to placebo with saline in the treatment of osteoarthritic knees [13]. A series of studies have recently been published showing promising effect of adipose-derived mesenchymal stem cells (AMSCs). By using AMSC, a large number of cells can be harvested from a small volume of tissue thereby avoiding the costly and time consuming process of expanding the cells in culture [5, 9].

Mesenchymal stem cells are thought to be able to activate and influence the microenvironment by serving as “a site-regulated drug store” [14]. Caplan and Correa use the term Medicinal Signaling cells (MSC), instead of mesenchymal stem cells, due to the in vivo qualities of those cells. The use of adipose-derived mesenchymal stem cells in treatment of OA has been of huge interest the past years [15, 16], and the complex regulatory issues involved in using enzymatic treated and/or expanded cells have led to the development of minimally manipulated tissue techniques [17]. The Lipogems system is one such system where the adipose tissue is micro-fragmented and washed free of blood residues. The resulting product is safe (FDA approval in 2016) and is said to be effective in the treatment of different pathologies [18], but level one evidence is lacking.

Initially, a pilot safety study was performed and no serious adverse effect was observed [19]. In this study, a positive result was found in 15 out of 20 patients. The pilot study was a prospective study, but not a randomized controlled study.

### Objectives {7}

With this study, we aim to investigate if treatment of patients with osteoarthritis of the knee with autologous, micro-fragmented adipose tissue prepared using the Lipogems system improves the patient reported health and function.

Hypothesis: Treatment of patients with osteoarthritis of the knee with autologous, micro-fragmented adipose tissue prepared using the Lipogems system leads to (1) improved patient-reported health seen as an increase in KOOS4 and (2) improved physical activity of the patient seen as an increase in the Tegner activity score.

Null hypothesis: There is no difference in patient-reported outcome or physical activity after treatment with autologous, micro-fragmented adipose tissue when compared to placebo treatment.

### Trial design {8}

The study is performed as a blinded, randomized controlled trial (RCT). Patients are individually randomized in two parallel groups in a 1:1 ratio:
The intervention group: Participants are treated with a 10-ml intra-articular injection of autologous, micro-fragmented adipose tissue.

## The control group: Participants receive a 10-ml intra-articular injection with isotonic saline (placebo).

## Methods: participants, interventions and outcomes

### Study setting {9}

The study will be performed at two centres in Denmark, Copenhagen University Hospital Hvidovre and Zealand University Hospital, as these two hospitals are the workplace of the authors.

### Eligibility criteria {10}

Patients with pain and functional impairment due to knee osteoarthritis are eligible for inclusion.

If the arthroplasty or sports surgeon, after clinical assessment, finds a patient eligible for inclusion, the patient is referred to the primary investigator for verbal information and written information concerning the trial. The patient is given the opportunity, on an informed basis, to decide whether he/she wants to participate in the trial and is informed of his/her right to at least 24 h of reflection before deciding. See Fig. 1 for patient flow diagram.

**Fig. 1 Fig1:**
[figure not shown]
Patient flow diagram. Patients assessed for eligibility are registered according to the consort requirements and will be presented in the final study paper in a consort flow diagram like this

All patients assessed by the primary investigator for eligibility are registered according to the consort requirements.

If a patient meets the inclusion criteria, and has signed the declaration of consent, baseline registration is recorded by the treating surgeon in a REDcap database designed specifically for the study. After recording baseline data, a survey is automatically sent to the patient by email. The survey includes baseline KOOS4, Tegner activity score and questions regarding work status.

The inclusion criteria are as follows:
* Age 18–70 years.* Kellgren-Lawrence score grades 2–3 in the tibiofemoral joint, either in the * medial, lateral or both compartments.* The patient must be expected to be able to attend follow-up examinations.* The patient must be able to speak and understand Danish.* The patient must be able to give informed consent.

Exclusion criteria are:
* Smoking (the patient must consent to being non-smoking 6 weeks before and 6 weeks after the procedure)* Varus or valgus malalignment of the knee > 5°* Laxity of the medial collateral ligament (MCL) or lateral collateral ligament (LCL) of 10° or more compared to the opposite knee* Knee instability and anterior-posterior laxity of 3 mm or above (compared to the opposite knee)* Preceding open surgery to the knee or fracture in the proximal tibia or distal femur* Extension deficit of the knee* Kellgren-Lawrence score grade 4 in any of the three compartments* BMI > 40* Terminal illness or severe medical illness: ASA score higher than or equal to 3

### Who will take informed consent? {26a}

If the arthroplasty or sports surgeon, after clinical assessment, finds a patient eligible for inclusion, the patient is referred to the primary investigator for verbal information and written information concerning the trial. The patient is given the opportunity, on an informed basis, to decide whether he/she wants to participate in the trial and is informed of his/her right to at least 24 h of reflection before deciding. See Fig. 1 for patient flow diagram.

All patients are assessed by the primary investigator for eligibility.

### Additional consent provisions for collection and use of participant data and biological specimens {26b}

All patients were informed verbally and by written information, that 2 ml of the micro-fragmented tissue is stored in a freezer at a temperature of – 81 °C for cell count and later analysis of bioactive markers. By the end of the project, any biological material left will be destroyed.

### Interventions

#### Explanation for the choice of comparators {6b}

The intervention group: Participants are treated with a 10-ml intra-articular injection of autologous, micro-fragmented adipose tissue.

The control group: Participants receive a 10-ml intra-articular injection with isotonic saline (placebo).

The aim of the study is to find out if the active treatment is better than no treatment. A saline injection was chosen as the comparator as it was considered the best alternative to mimick “no treatment” in a blinded setup.

#### Intervention description {11a}

Description of the active treatment:

The active treatment is an intra-articular injection with autologous, micro-fragmented adipose tissue prepared using the Lipogems® system.

Harvest of adipose tissue is performed in local anaesthesia under sterile conditions in the operating theatre. The patient is positioned supine, and the lower abdomen is used as donor site, and this is marked on the skin with a surgical marker. The area is approximately 8 cm (crania-caudal) × 20 cm (lateral) and situated just below the umbilicus. In patients, where tissue harvest from the abdominal area is not possible due to low fat mass or scarring from earlier procedures, harvest is performed from the lateral thigh area. Surgical cleaning is performed twice and a sterile draping is applied. The adipose tissue is prepared for harvesting by injection of tumescence using a disposable 17G blunt cannula connected to a suspension of 40 ml Carbocain 1%, 250 ml isotonic saline, 0.5 mg adrenaline and 10mmol Bicarbonate. Fifteen minutes after installation of the local anaesthesia, approximately 100-ml fat is harvested manually using a 13G blunt suction cannula connected to a Vaclock® 20-ml syringe via two stab punctures. At the end of the procedure, the skin is closed with a band aid, and the patient is given an elastic compression bandage to be used for 3–4 weeks or as long as the area of liposuction is sore and swollen.

The harvested fat is immediately processed in the Lipogems® processing kit, a disposable closed device that progressively and mechanically reduces the size of the adipose tissue clusters while eliminating blood residues with pro-inflammatory properties during constant irrigation. The entire process, carried out in one surgical step, is performed in complete immersion in physiological saline solution minimizing traumatic action on the important cell products. The resulting micro-fragmented tissue is collected in two 5-ml syringes to be re-injected in the patient’s knee joint.

Implantation of the graft is performed with the patient supine using two injections sites in order to reduce the risk of extra-articular injection. Local anesthesia with lidocaine 1% is given in the skin at the two injection areas. The first injection is in the intercondylar notch. On a 90° bend knee the lateral soft spot is located just lateral to the patella tendon and approximately 1 cm proximal to the tibial plateau. The syringe is introduced 2–4 cm perpendicular to the tibial axis aiming in the direction of the cruciate ligaments. To make sure the needle is positioned intra-articular, 1 ml of saline is injected; if there is any resistance to the injection, the needle is repositioned and the procedure done over again. Injection is performed using a 21-gauge syringe. The second injection is done with the knee in full extension. The syringe is introduced from lateral into the suprapatellar pouch posterior to the patella. Injection of 1 ml saline is repeated to ensure intra-articular position. At the end of the procedure the skin is closed with two band aids.

#### Criteria for discontinuing or modifying allocated interventions {11b}

The trial is a one-time intervention. The intervention cannot be discontinued or modified.

#### Strategies to improve adherence to interventions {11c}

Not applicable since it’s a onetime intervention.

#### Relevant concomitant care permitted or prohibited during the trial {11d}

Participants are allowed standard pain medication and physiotherapy. Any type of intra-articular injection or operation is not permitted and will lead to exclusion from the trial.

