### Outcomes {12}

#### Primary outcome

The primary outcome, the Knee injury and Osteoarthritis Outcome Score (KOOS_4_), is evaluated at 6 months after the intervention. See Fig. 3 for the study timeline.

The KOOS questionnaire was developed in the 1990s as an instrument to assess the opinion of patient’s with knee osteoarthritis about their knee and associated problems. Since the first publication in 1998, the psychometric properties of the KOOS have been assessed in more than twenty individual studies from all over the world. Furthermore, KOOS 1 year post surgery has been evaluated and compared to other instruments in several reviews [20–23].

KOOS4 constructs an average score for 4 out of the 5 KOOS subscale scores. It was first used by Frobell et al. in 2010 [24]. The fifth subscale concerning activities of daily living (ADL) is excluded in the KOOS 4 as the subscale is thought to add unwanted “noise” to the constructed outcome in active patients with few to none difficulties within ADL [23]. As the population of the trial is active patients, KOOS4 was chosen as the primary outcome.

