##### Failure

If the patient does not experience a clinically relevant improvement in KOOS_4_, the treatment is considered a failure, and this is registered at follow-up. A clinically relevant difference is estimated to be 10 points [24]. The number of patients experiencing failure of the treatment is recorded.

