### Concealment mechanism {16b}

Two researchers with no other connection to the trial is responsible for packing of continuously numbered, sealed, opaque envelopes. The allocation key is stored by and only accessible by the researcher who generated the allocation key. If a participant needs to know the allocated treatment ahead of trial termination, the study nurse will arrange this. Patients are still followed up according to the intention to treat principle.

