## Statistical methods

### Statistical methods for primary and secondary outcomes {20a}

Demographic parameters and outcomes at baseline are presented descriptively for the two groups. Between-group comparison of the primary and secondary outcomes is performed by use of relevant statistics according to the characteristics and distribution of the variables. The primary outcome, KOOS, is continuous and expected to be normally distributed. Due to the study design with repeated measurements at baseline, 3, 6 and 12 months, analysis will be performed using a linear mixed effect model.

All statistical testing will be performed at the two-sided 5% significance level, and 95% confidence intervals will be presented where appropriate. Statistical testing will take place after all participants have completed their 1year follow-up and sufficient time has been allowed for data entry and validation.

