### Methods in analysis to handle protocol non-adherence and any statistical methods to handle missing data {20c}

Prior to any analysis, missing data pattern will be investigated and reasons for missing data obtained and summarized where possible. The primary analysis will be conducted as an intention-to-treat analysis, which includes all participants with missing outcome data, unless there is clear evidence that its underlying assumption is inappropriate. Sensitivity analysis will be performed to assess the robustness of the results by imputing missing data using multiple imputations under both missing at random and missing not at random assumptions. Per protocol analyses will also be performed.

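### The concomitant-care rule excludes randomised participants from the trial after an injection or operation, which conflicts with the intention-to-treat primary analysis and loses outcomes that may be related to response

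*Protocol article*

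**What the plan says.** The section on concomitant care {11d} allows standard pain medication and physiotherapy and then states: "Any type of intra-articular injection or operation is not permitted and will lead to exclusion from the trial". The rule names the trial, not an analysis set. It is not confined to the study knee.

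The section on non-adherence and missing data {20c} states: "The primary analysis will be conducted as an intention-to-treat analysis, which includes all participants with missing outcome data". It plans sensitivity analyses by "imputing missing data using multiple imputations under both missing at random and missing not at random assumptions", and adds: "Per protocol analyses will also be performed".

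The section on concealment {16b} deals with a participant who learns the allocation early and says: "Patients are still followed up according to the intention to treat principle". Section {11d} has no matching sentence.

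The primary outcome, KOOS4, "is evaluated at 6 months after the intervention". Under Failure, a participant without a 10-point KOOS4 improvement is one for whom "the treatment is considered a failure, and this is registered at follow-up". The statistical methods section {20a} names the model: "Due to the study design with repeated measurements at baseline, 3, 6 and 12 months, analysis will be performed using a linear mixed effect model".

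**The concern.** Intention-to-treat means that everyone randomised is followed and analysed in the allocated arm, whatever happens later. A rule that puts a participant out of the trial because of something that happened after randomisation works against this. A site that follows section {11d} literally would stop follow-up, and the 6-month score would not exist.

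The loss is unlikely to be neutral. Participants enter with pain and functional impairment from knee osteoarthritis, and those whose symptoms persist are the likely ones to seek a further injection or an operation. The document does not say this, but it is a reasonable inference. If such events are commoner in one arm, removing those participants makes that arm look better than it is. The failure count is exposed in the same way: failure is judged from KOOS4 at follow-up, so a participant excluded after an operation may never be counted. Exclusions would also accumulate towards 12 and 24 months.

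**Working it through.** **The texts side by side.**

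| Section | Event | Consequence stated |
|---|---|---|
| Concomitant care {11d} | Injection or operation after randomisation | Excluded from the trial |
| Concealment {16b} | Participant learns the allocation | Follow-up continues under intention-to-treat |
| Missing data {20c} | Missing outcome data | Kept in the intention-to-treat analysis |
| Missing data {20c} | Non-adherence | Separate per-protocol analysis, additional to the primary |

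No section joins the first row to the other three. The conflict lies in the text and does not depend on the arithmetic below, which only shows what could be at stake.

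**Inputs from the Sample size section.** Difference 10 points, SD 15, power 0.90, two-sided; 98 patients required and 120 enrolled. The 5% level is from section {20a}.

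**The plan's own figure.** The normal approximation gives 48 per arm (96). With the t-test, power is 0.898 at 48 per arm and 0.904 at 49 per arm, so 49 × 2 = 98 is reproduced. With all 60 per arm analysed, power is 0.952. The dropout allowance is 120 − 98 = 22 patients.

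**Assumed inputs.** The protocol gives no rate of injections or operations, so every rate below is an assumption. So is ρ, the correlation between the 6-month outcome and being excluded; ρ = 1 means that exactly the worst scorers leave.

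**Formula.** If a fraction f of an arm leaves, the mean of those remaining rises by ρ × 15 × φ(z_f)/(1 − f), where z_f is the normal quantile of f. The ratio φ(z_f)/(1 − f) is 0.1086 at f = 5% and 0.1950 at f = 10%.

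*10% of saline and 5% of active leave.* The bias is ρ × 15 × (0.1950 − 0.1086) = ρ × 1.30 points.

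| ρ | True 10 points seen as |
|---|---|
| 0.3 | 9.6 |
| 0.7 | 9.1 |
| 1 | 8.7 |

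*Near-worst cases: everyone below one common KOOS4 threshold leaves (ρ = 1).* The active arm lies 10/15 = 0.667 SD higher, so fewer of its members fall below.

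- 10% of saline (z = −1.282) and 2.6% of active (z = −1.948): 10 − 15 × (0.195 − 0.061) = 8.0.
- 15% of saline (z = −1.036) and 4.4% of active (z = −1.703): 10 − 15 × (0.274 − 0.098) = 7.4.

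*Equal rates and equal selection in both arms.* The two shifts cancel and the bias is zero.

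All these figures compare completers at 6 months. They are not the planned mixed model.

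**What the planned model recovers.** I used large simulated samples, an assumed correlation of 0.5 to 0.7 between the 3- and 6-month scores, and the same two thresholds. If exclusion follows the 3-month score, completers show 8.2 to 9.0, while a likelihood-type estimate that uses the 3-month data returns about 10.0. If exclusion follows the 6-month score itself, that estimate is about 7.9 to 8.9, against 7.3 to 8.0 in completers.

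**The case against.** The strongest reply is that the missing-data section already keeps participants without outcomes in the intention-to-treat set. An excluded participant could then contribute data up to exclusion. The mixed model uses those data, and imputation under missing-not-at-random assumptions is aimed at just this kind of loss. Section {11d} also does not say that surveys stop, and the data collection section describes surveys sent automatically at every time point. This stands as mitigation. It does not settle the matter: for the 6-month endpoint the model has only baseline and 3 months to draw on, and the imputation is a sensitivity analysis that puts assumptions in place of scores that could have been collected.

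Some stronger readings are tempting but not supported:

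- *That intention-to-treat is impossible under this plan.* The missing-data section can be read as retaining these participants, so the texts conflict on a literal reading and need reconciling.
- *That the treatment effect will be understated by 2 points or more.* This needs assumed rates, the worst scorers leaving and a completers' comparison. The model's estimate is closer to the truth, and shows no bias if the 3-month score explains the loss.
- *That the trial loses its power.* The near-worst cases lose about 8 (6 + 1.5) and 12 (9 + 2.7) of 120 patients, inside the allowance of 22. Simulated completers' power there is about 88% and 83 to 84%, against a design target of 90%.
- *That injections and operations go unrecorded because the data table has no field for them.* A summary table in an article may leave this to the full protocol or case report form.

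The sentence on unblinded participants does not contradict section {11d}. It matters as a contrast: the safeguard was written for one event and not for the other.

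**Conclusion.** The concern holds as a conflict between the exclusion rule and the intention-to-treat primary analysis. Followed literally, the rule loses 6-month KOOS4 and failure status for participants whose loss is probably related to outcome, and this loss is avoidable.

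Its size cannot be known from the document. Among completers, a true 10-point difference would be seen as about 9.6 to 8.7 at assumed rates of 10% versus 5%, as 8.0 to 7.4 in the near-worst cases, and as 10 if rates and selection are equal. The planned model and imputation would reduce any bias by an amount that depends on how well the 3-month score predicts exclusion. The direction is also conditional: bias favours whichever arm loses more of its poor responders. If that is saline, a true benefit shrinks; if it were the active arm, the sign would reverse.

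The point deserves correction despite the uncertain size, because outcomes that were not collected cannot be recovered at analysis.

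**What to change.** Reconcile sections {11d}, {16b} and {20c}. State that a participant who receives an injection or operation stays in follow-up, still receives all KOOS surveys and is analysed as randomised in the intention-to-treat analysis. State that the event and its date are recorded, and that exclusion on this ground applies only to the per-protocol set. Failure is then judged for these participants from their own follow-up scores. Which concomitant care is permitted is left as it is.

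The cost is about one sentence in the protocol and, if not already captured, one recorded item. No extra patients or visits are needed, since the surveys are automated and the study nurse already telephones participants. The downside is that the intention-to-treat estimate then includes any effect of the additional treatment; the per-protocol analysis already planned addresses that question.
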